#### Quantitative data collection (step III)

Anticipated outcomes in patients will be measured before the intervention (T0) and six months after the start of the RbCCCM (T1). A self-administered questionnaire (30 min) will measure the patient’s perception of their experience of care during transitions between teams: responsiveness [75]: timeliness of access (4 items; α = 0.77), person-centred care (5 items, α = 0.67), quality of communication (5 items, α = 0.85), self-management capacity based on the heiQ validated in oncology [76], involving: emotional distress (6 items; α = 0.77), wayfinding in the health system (5 items, α = 0.85), social support and integration (5 items, α = 0.85), as well as quality of life SF12 (12 items, α = 0.83) [79]. Though the project does not include an economic evaluation, data related to some costs will be collected, notably among men with prostate cancer [80], using a generic instrument and a diary to report costs of using health care (time, transport costs, non-reimbursed medication costs, lost income). This data will provide the basis for economic analysis in a future study. Sociodemographic and clinical data will be collected: age, gender, comorbidity, cancer type, health status, chronic diseases [81], survivorship profile [82].

Anticipated outcomes among professionals will be measures before the intervention (T0) and 6 months after the start of the RbCCCM (T1), an interval based on feasibility in a demonstration project. A self-administered questionnaire (30 min) with validated psychometric properties will be employed: SCOP scope of practice (26 items, α = 0.89) [83], teamwork (5 items, α = 0.84) [84], team environment (19 items, α = 0.88–0.93) [85], shared leadership (13 items, α = 0.66) [86]. The density and centrality of intra- and inter-team links will be measures using social network analysis [87]. Data on sociodemographic characteristics will also be collected (age, gender, profession, practice setting, years of experience).

#### Quantitative data analysis (step III)

Descriptive statistical analyses, comparative analyses based on data type (t-test, Chi2, ANOVA, ANCOVA), and regression analyses (multilevel logistic and linear because of the structure and hierarchy of data) will be conducted. These will enable us to determine the association (positive, negative or neutral) between the RbCCCM, professional practice, and the care experience of cancer survivors during transitions, while controlling for certain potentially confounding individual and organizational variables. The threshold for significance will be 5%.

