**Methods/design:**

This multiple case study using a sequential mixed-methods design rests on a theory-driven realist evaluation approach to understand how transitions might be improved. The cases are two health regions in Quebec, Canada, defined by their geographic territory. Each case includes a Cancer Centre and three Family Medicine Groups selected based on differences in their determining characteristics. Qualitative data will be collected from document review (scientific journal, grey literature, local documentation), semi-directed interviews with key informants, and observation of care coordination practices. Qualitative data will be supplemented with a survey to measure the outcome of the coordinated model among providers (scope of practice, collaboration, relational coordination, leadership) and patients diagnosed with breast, colorectal or prostate cancer (access to care, patient-centredness, communication, self-care, survivorship profile, quality of life). Results from descriptive and regression analyses will be triangulated with thematic analysis of qualitative data. Qualitative, quantitative, and mixed methods data will be interpreted within and across cases in order to identify context-mechanism associations that explain outcomes.

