### Demonstration project

The design for analyzing the implementation (Step II) and evaluation of outcomes (Step III) is a multiple case study [54] based on qualitative and quantitative data [55]. The design is appropriate to understanding a contemporary phenomenon (the RbCCCM) as it manifests in the real world where it may be influenced by multiple changing and interdependent factors and contextual challenges. A case is defined as the cancer care trajectory in order to understand how the RbCCCM mobilizes members of specialized cancer care teams and primary care teams during transitions.

The selection of cases is based on theory [54] to represent real-world differences [56] in terms of geographic location (the territorial expanse served; rural/semi-urban/urban areas), mission (academic or not), the size and diversity of care teams and their interest in being involved in the RbCCCM demonstration project. Units of analysis are the hospital-based cancer care teams and the FMGs of two Integrated Health and Social Service Centres (3/11 FMGs + one hospital in Saguenay-Lac-Saint-Jean (Case 1); 3/31 FMGs + one hospital in the Montérégie (Case 2). The selection of cases is also influenced by feasibility and our knowledge of these establishments gained through their participation in prior research we conducted on cancer care [8, 37, 38, 57–63], on primary care [64, 65], as well as on organizational factors that influence the care experience of people having received a cancer diagnosis [38].

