#### Step III - Outcomes of the RbCCCM

This stage aims to understand the outcomes of the RbCCCM in patients and professionals in each of our cases. It uses experimental approaches to verify our working hypothesis that the RbCCCM will have a positive impact on professional practice and the care experience of cancer survivors (patient-reported experience). The impossibility, for ethical and professional reasons, of conducting a randomized controlled trial calls for a pragmatic before-and-after design with delayed intervention (6-month follow-up) where teams in one case will provide usual care (control segment) while teams in the other case are implementing the components of the intervention (intervention segment). This step will answer Question 3.

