#### Sample (step III)

The sample size is calculated according to our previous studies on the responsiveness of cancer care [75] and the Health Education Impact Questionnaire (heiQ) scoring for self-management capacity [76]. Given that scores on the scales range between 1 and 4, an average score of 2.3 and a difference of 0.3 are reasonable. One hundred patients per case will be recruited, based on anticipated attrition of about 10%. If we consider the heiQ distress score, this sample size would enable us to detect a 0.3 difference between measures at 2 time points in a same group, and between groups, with a standard deviation of 0.71 and confidence interval of 0.80.

The sample size will include about 50 professionals per case (100 total) including personnel in the FMGs and the cancer care teams. The minimum response rate based on our previous studies is anticipated at 40%. Limitations related to the small sample size will, as is common in case studies, be compensated by the qualitative data described in Step II [77].

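### Tests that ignore the family medicine group stand beside multilevel models under one 5% threshold, with no statement of which decides and only six groups behind the between-case contrast

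*Protocol article*

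**What the plan says.** All of the following is in the protocol article.

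- **Quantitative data analysis (step III)** lists two families of methods in one sentence. The first family has no FMG term as named: "comparative analyses based on data type (t-test, Chi2, ANOVA, ANCOVA"). The second is chosen for the clustering: "regression analyses (multilevel logistic and linear because of the structure and hierarchy of data) will be conducted". The next sentence gives both families the same job, which is to establish whether the care model is associated with professional practice and patient experience. One threshold follows for all of them: "The threshold for significance will be 5"%.
- **Demonstration project** fixes the upper levels: "3/11 FMGs + one hospital in Saguenay-Lac-Saint-Jean (Case 1") and "3/31 FMGs + one hospital in the Montérégie (Case 2"). The abstract describes each case as having "three Family Medicine Groups selected based on differences in their determining characteristics".
- **Step III - Outcomes of the RbCCCM** puts one whole case in each arm: "teams in one case will provide usual care (control segment") while the other case implements the intervention.
- **Sample (step III)** sizes the patient survey: "One hundred patients per case will be recruited, based on anticipated attrition of about 10"%. It uses a difference of 0.3, a standard deviation of 0.71 and a figure of 0.80, which is called a confidence interval and which I read as power.

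The article gives no ICC.

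**The concern.** The analysis section recognises dependence between patients and then also plans tests that assume there is none, with the same inferential role and the same threshold. If a t-test and a multilevel model disagree, the text does not say which result stands.

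The multilevel label does not settle the matter by itself. Each hospital coincides with its case, so the only replication above the patient is three FMGs per arm. They were chosen to differ, which makes a between-FMG variance of zero less plausible. With 4 degrees of freedom that variance is poorly estimated, and a large-sample test of the case contrast is too liberal. If the model has an FMG intercept but no FMG-by-time term, FMG differences in change are left out, and the contrast in change behaves much like the plain t-test.

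At stake are intervals that are too narrow and associations declared too often. Step IV then takes the Step III outcomes as things to be explained by context and mechanism, so a spurious association would be carried into the refined theory.

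**Working it through.** **Inputs from the article.** Two cases with 3 FMGs each; 100 patients per case with about 10% attrition, so about 90 completers; difference 0.3; SD 0.71; 5% threshold.

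**Assumptions.** Two-sided testing. Completers spread equally, so m = 30 per FMG. FMG ICC of 0.01, 0.02 or 0.05; for change scores, read this as the ICC of change. The simulations use linear outcomes and equal FMG sizes. Logistic models were not simulated.

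**1. The stated sample size.** n per arm = 2 × (1.96 + 0.842)² × 0.71² / 0.3² = 87.9, so 88. Allowing for 10% attrition, 88 / 0.9 = 97.8, so 98, against 100 stated. Power with 90 per arm is 0.81. The figure is reached with no term for clustering.

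**2. Tests that ignore the FMG.** The design effect is DE = 1 + (m − 1) × ICC. The false-positive rate is 2 × [1 − Φ(1.96 / √DE)].

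| ICC | DE | 1.96/√DE | Formula | Simulated |
|---|---|---|---|---|
| 0.01 | 1.29 | 1.726 | 8.4% | 8.5% |
| 0.02 | 1.58 | 1.559 | 11.9% | 12.0% |
| 0.05 | 2.45 | 1.252 | 21.0% | 21.2% |

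**3. Analyses that include the FMG.** Simulated null trials, 2 arms × 3 FMGs × 30 patients, no case-level variance:

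| ICC | REML, read against z | REML, read against t on 4 df | t-test of FMG means, 4 df |
|---|---|---|---|
| 0.01 | 5.8% | 0.9% | 5.0% |
| 0.02 | 7.2% | 1.5% | 5.0% |
| 0.05 | 9.6% | 2.8% | 5.0% |

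REML on 4 df is conservative because the FMG variance is often estimated as zero (in about 45%, 35% and 18% of trials at the three ICCs). The last two columns are therefore not interchangeable. Kenward-Roger degrees of freedom were not simulated.

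**4. Wider ICC range.** At ICC 0 the plain t-test gives 5% and REML with z gives 3.8%. At ICC 0.10 they give 33% and 11%.

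**5. Professionals.** If the 50 per case are those invited and 40% respond, there are about 20 responders in 4 teams (three FMGs and the hospital), or 5 per team. For ICC 0.01 to 0.05, tests that ignore the team give 5.5% to 7.4%, and REML with z gives 4.7% to 5.8%.

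**6. Power for 0.3 on 4 df (FMG-mean test of change).** SD of change = 0.71 × √(2(1 − r)), where r is the assumed T0–T1 correlation. This is 0.71 at r = 0.5 and 0.577 at r = 0.67. The noncentrality is 0.3 / (SD of change × √(2 × DE / 90)). At r = 0.5 and DE = 1 it is 0.3 / 0.1058 = 2.83, set against a critical value of 2.776.

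| ICC of change | Power, r = 0.5 | Power, r = 0.67 |
|---|---|---|
| 0 | 57% | 74% |
| 0.01 | 48% | 64% |
| 0.02 | 41% | 56% |
| 0.05 | 29% | 40% |

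**7. One case per arm.** With FMG ICC 0.02 and an assumed case-level ICC of 0.01, 0.02 or 0.05, the FMG-mean test on 4 df gives false-positive rates of 9%, 13% and 23%.

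**The case against.** The strongest reply is that the article already names the hierarchy and chooses multilevel models for it. The degrees-of-freedom method, REML or ML, and the exact random terms normally belong in an analysis plan, which is not at hand. The article names neither a z test nor an intercept-only model. This stands: the absence of a small-sample method is not an error in the article, and the REML rates above apply only if the model is read against z. The reply does not remove the point, because the mixing of the two families under one threshold is printed.

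A reader might infer that the study's true false-positive rate is 6% to 21%. The documents do not support that. They give no ICC, and the two ends of that range belong to different methods: the multilevel model read by REML does not reach 21%. Nor do the rates cover every Step III test. They apply to the between-case contrast in patients. Inflation is smaller for professionals. In a paired comparison within one case a stable FMG effect cancels, so only FMG differences in change matter.

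A reader might also infer that a small-sample method restores 5%. It does so only if there is no case-level variance, which a design with one case per arm cannot show.

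Finally, this is a demonstration project whose survey results are combined with qualitative data. That lowers the stakes but does not change the standard errors.

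**Conclusion.** The point holds in a limited form. The analysis section acknowledges clustering, gives tests that ignore it the same inferential role and threshold as the multilevel models, and does not say which decides. The design leaves six FMGs and 4 degrees of freedom for the between-case contrast.

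The size depends on an ICC that has to be assumed. For patients at ICC 0.01 to 0.05, the nominal 5% becomes about 8.5% to 21% if the FMG is ignored, and about 6% to 10% under REML read against z. At ICC 0 there is no inflation. The change is worth making before analysis. Confidence is medium, because the ICC is unknown and the SAP may already settle the deciding model.

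**What to change.** In Quantitative data analysis (step III):

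1. Restrict t-test, Chi2, ANOVA and ANCOVA without an FMG term to description.
2. Name one deciding analysis for the between-case contrast. This can be a multilevel model with patient, FMG and FMG-by-time terms and a small-sample degrees-of-freedom correction such as Kenward-Roger. It can instead be a t-test on 4 degrees of freedom comparing the three FMG mean changes in one case with the three in the other. Choose one in advance, since they are not equivalent. Treat the professional scales in the same way, by team.
3. Report estimates with the intervals from that analysis.
4. State that each arm is a single case, so no FMG-level correction separates the effect of the care model from case-level differences.

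The cost in wording and software is small, but the cost in precision is not. Power for 0.3 on 4 degrees of freedom is about 57% to 74% with no FMG-by-time variance, and about 29% to 64% at an ICC of change of 0.01 to 0.05. The 0.80 in Sample (step III) should carry that qualification.

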Case 1 is an academic health centre that has deployed, since 2010, an intervention in FMGs aimed at improving care coordination for people with chronic diseases (other than cancer) through nurse case managers and group sessions to support self-management [64, 65]. In this case, the RbCCCM might be integrated into these existing practices, with cancer treated as a chronic disease [13]. Case 2 has, since 2001, deployed efforts in specialized cancer care (nurse navigators, implementation of a cancer care network, development of an integrated centre, introduction of the clinician advisor role) [37, 38, 60, 63, 66, 67]. The two cases offer possibilities for analyzing the RbCCCM and better understanding variations in implementation and outcomes. The realist approach is employed for its pragmatic and participatory principles that help to discover what works (and what doesn’t), how it works, for whom, and under what conditions. This approach is suited to analysis of complex interventions [48].

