#### Validity (step III)

Internal validity rests on use of questionnaires with validated psychometric strengths, sample size, and control of confounding variables in the regression models. Results will be generalizable to other settings with characteristics similar to the cases in the study.

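### With one region per segment, regression on case-level organizational variables cannot supply the confounding control claimed for Step III; a group-by-time contrast with a stated parallel-trends condition is needed

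*Protocol article*

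**What the plan says.** The article's Demonstration project section defines two cases: "3/11 FMGs + one hospital in Saguenay-Lac-Saint-Jean (Case 1); 3/31 FMGs + one hospital in the Montérégie (Case 2"). They were selected to differ in location, mission and team make-up. "Case 1 is an academic health centre that has deployed, since 2010, an intervention in FMGs aimed at improving care coordination" for chronic diseases other than cancer. Case 2 has been building up specialised cancer care, including nurse navigators and a cancer network, since 2001.

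Step III rules out randomisation and "calls for a pragmatic before-and-after design with delayed intervention (6-month follow-up"), in which "teams in one case will provide usual care (control segment) while teams in the other case are implementing the components of the intervention (intervention segment"). On timing, "Anticipated outcomes in patients will be measured before the intervention (T0) and six months after the start of the RbCCCM (T1").

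The sample-size section aims to detect a difference of 0.3 (SD 0.71) between two time points in one group, and between groups, with 100 patients per case.

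The analysis section lists "comparative analyses based on data type (t-test, Chi2, ANOVA, ANCOVA") and multilevel logistic and linear regression, "while controlling for certain potentially confounding individual and organizational variables", at a 5% threshold. The Step III validity section then rests internal validity on validated questionnaires, sample size and "control of confounding variables in the regression models".

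**The concern.** Each segment is a single region, and the regions were picked because they differ. The known differences are earlier coordination and self-management programmes. They bear directly on the outcomes measured: access, communication, finding one's way in the health system, self-management and teamwork.

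The validity section presents regression adjustment as the answer to confounding. For anything that is constant within a case, regression cannot do this. The two contrasts named in the sample-size section each mix the RbCCCM effect with something else, and the article names no contrast that combines them. A result below 5% from either one could be read as an RbCCCM effect when it reflects the region or the passage of time. Step IV then carries the Step III outcomes into its context-mechanism-outcome configurations.

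**Working it through.** **1. The plan's own figure.** Inputs from the sample-size section: difference 0.3, SD 0.71, attrition about 10%. The 0.80 there is labelled a confidence interval and is read here as power. Two-sided 5% is assumed.

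n = 2 × 0.71² × (1.960 + 0.842)² / 0.3² = 87.9, so 88 per case; 88 / 0.9 = 97.8, so 98. The stated 100 is reproduced. Power at 90 evaluable per case is 0.81. This treats patients as independent and assumes no region effect.

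**2. What each contrast estimates.** Let *a* be the stable region difference, *g* the common change over six months, *h* the extra change specific to the intervention region, and *d* the RbCCCM effect.

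| | T0 | T1 |
|---|---|---|
| Control case | μ | μ + g |
| Intervention case | μ + a | μ + a + g + h + d |

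- Between cases at T1: d + a + h
- Before-after in the intervention case: d + g + h
- Group-by-time (difference-in-differences): d + h

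The third contrast removes *a* and *g*. None removes *h*, and with a single pre-measurement the data cannot show whether *h* is zero.

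**3. What regression can add (rank of the design matrix).**

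- T1 only, with intercept, region and treatment: rank 2 for 3 parameters. Treatment is region.
- T0 and T1, with intercept, region, time and treatment: rank 4 of 4. The effect is estimable.
- The same plus region-by-time: rank 4 of 5. It is aliased with treatment.
- The same four plus an organizational covariate constant within a case: rank 4 of 5. It adds nothing beyond region.

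A multilevel model does not change this: two regions leave no degrees of freedom for between-region variance once treatment is fitted.

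**4. Size for an unadjusted T1 comparison.** The documents give no ICC, so 0.01 to 0.05 is assumed. With 90 per case, the design effect is DE = 1 + 89 × ICC, and actual type I error = 2[1 − Φ(1.96/√DE)].

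| Region ICC | DE | Actual type I error |
|---|---|---|
| 0.01 | 1.89 | 15% |
| 0.02 | 2.78 | 24% |
| 0.05 | 5.45 | 40% |

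**5. Size for the group-by-time contrast.** Assume a within-patient correlation of 0.5, and let a share *s* of the region variance be specific to the period. The variance inflation is 1 + 90 × s × ICC / [(1 − ICC)(1 − 0.5)].

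| s | ICC 0.01 | ICC 0.05 |
|---|---|---|
| 0 | 5% | 5% |
| 0.2 | 9% | 25% |
| 0.5 | 16% | 41% |

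The contrast holds its 5% level if region differences are stable, and loses it as they drift.

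**The case against.** A reader might infer that the RbCCCM effect cannot be separated from region at all. The documents do not support that. The design has a T0 measurement and a concurrent usual-care segment, so stable region differences can be removed. The programmes dating from 2010 and 2001 are long-standing and largely of that kind.

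Nor are all organizational variables case-level. There are three FMGs in each case, and FMG variables that vary within a case can be adjusted for, as can individual variables. The article speaks only of certain variables and does not say they are case-level.

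The analysis list also includes ANCOVA and multilevel models, and nothing says that a T1-only t-test is the effect test. The 15% to 40% range is therefore not the error rate of the planned analysis. The article claims an association, concedes that the sample is small, and limits generalisation to similar settings. Model details are commonly left to a full protocol or analysis plan.

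All of this stands, and it lowers the severity. It does not rescue the validity claim, which is stated without qualification and fails for case-level variables and region-specific change. The contrasts that the article does name, when sizing the study, are the two that absorb region or time. ANCOVA on T0 is not a full substitute in non-randomised groups: it leaves (1 − b) × a of the stable difference, where b is the within-case slope of T1 on T0.

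**Conclusion.** The concern holds in limited form. Neither the simple between-case nor the simple before-after comparison isolates the RbCCCM effect, and adjustment for variables constant within a case cannot repair that. A group-by-time contrast removes time-constant region differences. Region-specific change over the six months remains fully aliased with the RbCCCM, and parallel trends cannot be tested with one pre-measurement. The Step III validity section therefore claims more control than the design can give.

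The aliasing follows from the design and needs no assumed figure. The error rates are illustrations resting on assumed ICCs, period-specific shares and a within-patient correlation of 0.5. Severity: should fix.

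**What to change.** **Quantitative data analysis (step III).** Make the group-by-time (difference-in-differences) contrast between the intervention segment and the concurrent control segment the effect analysis. Include patient covariates measured at T0 and take FMG clustering into account. State that T0 and T1 cover the same calendar window in both cases. This needs saying because T1 is now anchored to the start of the RbCCCM, which comes later in the delayed case. Label the simple t-test, Chi2 and ANOVA results and the within-case before-after results descriptive. Do not present case-level covariates as confounding control.

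**Validity (step III).** State that the estimate is conditional on these two cases and on an untestable parallel-trends assumption, and that regression does not control region-by-time confounding.

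**Cost.**

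- The validity claim becomes more modest.
- T0 and T1 responses must be linkable. The procedure section calls the questionnaires anonymous and mentions an access code only for online completion, so an access or study code is needed for every patient.
- Precision is lower because there are only six FMGs. Even with independent patients, a change-score contrast needs 87.9 × 2(1 − r) patients per case before attrition: 124, 88 or 53 at an assumed within-patient correlation r of 0.3, 0.5 or 0.7. The planned 100 per case suffices only if r is about 0.5 or more.
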